#### Independent variables

The models draw on maternal demographic information and clinical data obtained at the time of eoPE diagnosis, including laboratory parameters, angiogenic biomarkers (sFlt-1/PlGF), and ultrasound findings. Below, the predictor variables used in each specific model are described in detail:

R model features: pulsatility index in the middle cerebral artery < percentile 5, gestational age at PE onset, number of antihypertensive administrated drugs, pulsatility index of the right uterine artery, previous PET model features: PlGF < percentile 5, sFlt-1/PlGF clinical classification, weight, personalized percentile of estimated fetal weight, pulsatility index of the left uterine artery, chronic hypertension and multiples of the median of the mean pulsatility index of the uterine arteriesHA model features: sFLt1 > percentile 95, PlGF clinical classification, PlGF < percentile 5

The models do not incorporate information related to the care center or socioeconomic status. They also do not include data on perinatal care; however, the study does collect the main perinatal outcomes for descriptive purposes. The complete set of variables collected for this study is detailed in Additional file 1.

### Study regimen

The study will follow the steps outlined in Fig. 2. First, pregnant women who meet the eligibility criteria will be identified at each participating center. They will receive both verbal and written information explaining the purpose and procedures of the study and will be invited to participate. After consent, the investigator will register the case in the REDCap™ database [33], hosted by the Research Institute of Hospital 12 de Octubre (i + 12), by selecting the appropriate center in the “Data Access Group,” which automatically generates a unique study identifier. All relevant clinical, analytical, angiogenic, and ultrasound data, from early pregnancy through delivery, will be collected and entered into the corresponding REDCap™ sections. Only once delivery has occurred will the clinician access the web application to obtain the model predictions and complete the semi-quantitative assessment, following the procedure detailed in the “Web Application” section.

**Fig. 2 Fig2:**
[figure not shown]
Study regimen including recruitment, data collection, and models validation

### Data collection

Data collection constitutes a critical phase of the study, as the quality and completeness of the information recorded will directly determine the robustness and validity of the subsequent external validation analyses. Study data are entered and managed is performed through a dedicated database developed for this purpose on the REDCapTM platform. It allows participating centers to create and complete electronic case report forms in real time and supports data import and export in multiple formats, including Microsoft Excel, PDF, SAS, Stata, R, and SPSS.

The designated clinician at each participating center will be responsible for recording all patient data in REDCap™, covering the period from the start of pregnancy until delivery. Each participant will be assigned a unique identification code that decouples clinical data from personally identifiable information. The linking file containing the correspondence between study codes and personal identifiers will be stored securely and accessible only to a limited number of authorized persons. Thus, the data complies with the Personal Data Protection and Guarantee of Digital Rights and Regulation (EU) 2016/679 of the European Parliament and of the Council of April 27, 2016 on Data Protection (GDPR).

In this sense, the first and last sections of the database are particularly important and are described in detail in Additional file 1. In the first section (“Patient ID”), the clinician must enter the patient’s medical record number (MRN), which is immediately encrypted to ensure full anonymization. The clinician must also confirm that the inclusion and exclusion criteria are met and record the date on which informed consent was signed.

In the final section (“Semi-quantitative assessment”), a link to the web application is provided. The appearance of the application interface is shown in Additional file 2. Once the data used by the models and the delivery information have been entered into the database, the clinician can access the application to obtain the model outputs and complete the semi-quantitative assessment. Both the model outputs and the clinicians’ responses will be automatically stored in this section under the corresponding patient’s record. This retrospective appraisal minimizes optimism bias and allows the evaluation to reflect the clinical value of the predictions rather than responses influenced by the models themselves.

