### Models’ validation strategy

An analysis will be conducted after the inclusion of the first 100 participants to perform an initial external validation of the predictive models. This validation will include both quantitative and semi-quantitative assessments:

The quantitative evaluation will focus on the diagnostic performance of the predicted risks, including the estimation of sensitivity, specificity, positive and negative predictive values, discrimination using the area under the ROC curve, calibration using the Hosmer–Lemeshow test, and clinical utility assessed through decision curve analysis.The semi-quantitative evaluation will consider clinicians’ perceptions of the information provided by the models. After reviewing the model’s information, they will be asked to answer four questions to assess the perceived usefulness and potential clinical impact of the predictions: (1) overall appreciation of the information (“I like it / I don’t like it”); (2) whether this information would have influenced their decision regarding corticosteroid administration (“No / Yes, I would have administered them earlier / Yes, I would have administered them later”); (3) whether it would have modified their management of hospitalization between diagnosis and delivery (“No / Yes, I would have extend the duration of hospitalization / Yes, I would have reduced it”); and (4) whether it would have changed their decision about the timing of delivery (“No / Yes, I would have indicated delivery earlier / Yes, I would have delayed delivery”).

Following this first phase, the ML training methodology will be replicated incorporating the information from the initial 100 cases, and the updated models will then be applied prospectively to the next 100 participants. This “re-training” methodology begins with a preprocessing stage, which includes missing-value imputation using MissForest, outlier removal, standardization of numerical variables with Standard Scaler, and encoding of categorical variables using OneHot and Label encoding [34]. Subsequently, model training is carried out using genetic algorithms within a multi-objective framework. These algorithms are non-deterministic, can be adaptive, and often benefit from parallel computation, enabling them to search for high-quality approximate solutions [35].

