After completing recruitment of 200 patients, a final validation will be performed, formally comparing the discriminative performance of the original and retrained models using the DeLong test for paired ROC curves. Bootstrap resampling will also be considered to derive more robust confidence intervals for key performance metrics, ensuring a stable evaluation of model behavior across samples. In parallel, the semi-quantitative responses from clinicians will be compared between the two phases, providing both an objective and a subjective assessment of model performance and clinical usability.

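### The post-delivery clinician survey is answered with the outcome known, so it cannot be said to reflect the predictions' clinical value at the time of decision

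*Protocol article*

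**What the plan says.** Study regimen fixes the order of events: "Only once delivery has occurred will the clinician access the web application to obtain the model predictions and complete the semi-quantitative assessment". Data collection adds a precondition: "Once the data used by the models and the delivery information have been entered into the database, the clinician can access the application". The same section says who enters the data: "The designated clinician at each participating center will be responsible for recording all patient data in REDCap™".

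Models' validation strategy sets four questions. The first is a like/dislike item. The other three are counterfactual and ask whether the information would have altered corticosteroid administration, hospitalization and delivery; the last asks "whether it would have changed their decision about the timing of delivery".

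Data collection gives the rationale: "This retrospective appraisal minimizes optimism bias and allows the evaluation to reflect the clinical value of the predictions". The rest of that sentence contrasts this with answers shaped by the models themselves.

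Table 1 and Workflow send a woman with low R risk straight to the survey. T and HA are run only when R exceeds 0.5. At the end of the study, "the semi-quantitative responses from clinicians will be compared between the two phases", and the article presents this as the subjective side of assessing performance and usability.

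**The concern.** Two things are run together in the rationale. Hiding predictions until delivery stops them from steering care, which keeps the outcomes clean for the quantitative validation. It does not make the later rating a measure of value when the decision was open. A clinician who knows the delivery date can hardly say whether steroids would have been given earlier or later without using that date.

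Clinical usefulness is named in the primary objective, and the Abstract describes the survey as physicians' assessment of clinical utility. If the Data collection sentence stands, readers may take the responses as evidence of usefulness at diagnosis, and a change between phases as evidence that retraining made the tool more useful. The responses alone support neither conclusion.

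**Working it through.** **What the rater knows.** Delivery information must be entered before the application opens. The T outcome (delivery within 7 days of diagnosis) is therefore settled at rating. R and HA outcomes are known at least up to delivery; the text does not say how later postpartum events are handled. It describes no rating made before the outcome and no rater blinded to it.

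**The plan's own figures.** No stated figure concerns the survey. The sample-size figures, which supply the event rates used here, reproduce: T 7 × 10 / 0.5 = 140; R 5 × 10 / 0.4 = 125; HA 3 × 10 / 0.2 = 150.

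**Predictions that turn out wrong.** Inputs are the simplified models' sensitivity and specificity (Background) and the incidences (Sample size estimation). Share correct = sensitivity × incidence + specificity × (1 − incidence).

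- R: 0.60 × 0.40 + 0.74 × 0.60 = 0.240 + 0.444 = 68.4% correct, so 31.6% wrong.
- T: 0.68 × 0.50 + 0.86 × 0.50 = 77% correct.
- HA: 0.92 × 0.20 + 0.52 × 0.80 = 60% correct.

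The T and HA values are for all women. Those models are run only in R-high women, whose incidences the article does not give.

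**Who is shown what.** Per 100 women, R gives 24.0 true positives, 16.0 false negatives, 44.4 true negatives and 15.6 false positives. R-high is 24.0 + 15.6 = 39.6 and R-low is 60.4. About 60 in 100 are thus rated without the T output, although T is the model that addresses delivery timing.

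Sensitivity to the assumed incidence, with R at 60%/74%:

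| Incidence | R wrong | R-low |
|---|---|---|
| 30% | 0.3 × 0.40 + 0.7 × 0.26 = 30.2% | 0.3 × 0.40 + 0.7 × 0.74 = 63.8% |
| 40% | 31.6% | 60.4% |
| 50% | 0.5 × 0.40 + 0.5 × 0.26 = 33.0% | 0.5 × 0.40 + 0.5 × 0.74 = 57.0% |

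**How far hindsight could carry into the phase comparison.** This is an illustration for the like/dislike item only, with assumed probabilities of liking a right prediction (a) and a wrong one (b). Approval = a × accuracy + b × (1 − accuracy). Phase 1 accuracy is 68.4%, and a 10-point gain in phase 2 is assumed. The shift is 0.10 × (a − b). Power is for 100 versus 100 at an assumed two-sided 0.05, ignoring clustering.

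| a / b | Correlation of liking with correctness | Approval, phase 1 to phase 2 | Shift (points) | Power |
|---|---|---|---|---|
| 0.7 / 0.7 | 0 | 70.0% to 70.0% | 0 | not applicable |
| 0.8 / 0.5 | 0.31 | 70.5% to 73.5% | 3 | 7% |
| 0.9 / 0.2 | 0.70 | 67.9% to 74.9% | 7 | 19% |
| 1 / 0 | 1.0 | 68.4% to 78.4% | 10 | 36% |

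The 95% half-width for a difference near 68.4% is 1.96 × √(2 × 0.684 × 0.316 / 100) = 12.9 points, again before clustering.

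**Shift through the R-high share.** With h the R-high share and p(H), p(L) the response rates in R-high and R-low women, the pooled rate is h × p(H) + (1 − h) × p(L). It changes by Δh × (p(H) − p(L)) even when neither group's answers change. If R sensitivity rose to the 70% of the 25-variable version at the same specificity, h would be 0.28 + 0.156 = 43.6%, up 4.0 points. With an assumed 30-point gap between groups, the pooled rate moves 0.040 × 30 = 1.2 points. The effect is small here, but it does not come from any change in perceived usefulness within either group.

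**The case against.** The plan has real defences. It claims to limit optimism bias, not all bias. It calls the survey post-hoc, lists it as a secondary objective about satisfaction, and describes the responses as perceived and subjective. It assigns clinical utility to decision curve analysis and the formal test of retraining to the DeLong comparison, neither of which the ratings touch. Giving R-low women no T or HA output is the intended cascade, so the survey does rate what the tool would deliver. Tabulation detail may properly sit in an analysis plan that is not shown. All of this stands and limits the weight of the point. It does not rescue the statement that the appraisal reflects clinical value.

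A reader might infer that the survey largely re-measures whether each prediction was right. The document does not support that. The correlation in the illustration runs from 0 to 1 on assumed inputs, and an approval rate equal to accuracy (68%) is only the extreme case. It also fits only the like/dislike item, because the other three questions have no approval rate: a correct prediction that matches what was done may well earn a No.

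A reader might also infer that the plan attributes a between-phase change to retraining. It says only that the responses will be compared.

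**Conclusion.** The point holds in a limited form. The responses are outcome-aware, and the rationale in Data collection credits them with a property that the design does not give. On the article's own rates, about 32% of R predictions would prove wrong (30% to 33% for incidence from 30% to 50%), and about 60% of women (57% to 64%) would be rated on R output alone. These figures assume that the development sensitivity and specificity carry over to the new centres and apply at the 0.5 cut-off, and that the R outcome is known by the time of rating. The strength of hindsight is unknown.

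The phase comparison mixes perceived usefulness with accuracy, case mix and R-high share, and at 100 versus 100 it is imprecise (about ±13 points). The AUC, sensitivity, specificity and decision curves are unaffected. This is a correction to interpretation and reporting; the validation itself does not fail.

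**What to change.** 1. Replace the Data collection claim with two statements: predictions are withheld until delivery so that they cannot influence management, and ratings are therefore made with knowledge of the outcome.
2. Report every survey item by prediction correctness (true and false positives and negatives), and separately for R-low women (R only) and R-high women (R, T and HA). For R, the four cells already contain this split: the positives are R-high and the negatives R-low.
3. Present the phase comparison as descriptive, with intervals that allow for clustering by centre or rater. If each centre has one rater, the two coincide and one term is enough. Do not adjust for correctness: it lies on the path from retraining to rating, so adjusting would remove part of any real benefit.
4. Rest the clinical-usefulness conclusion on the planned decision curve analysis and describe the survey as acceptability.

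Predictions and responses are already stored per patient, so no new data and no change in care are needed. The cost is a more modest claim and sparser cells. With about 16 false negatives per 100 women, a proportion near 50% has a half-width of 1.96 × √(0.25 / 16) = 24.5 points, so these tables can describe but not test.

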### Models’ validation strategy

An analysis will be conducted after the inclusion of the first 100 participants to perform an initial external validation of the predictive models. This validation will include both quantitative and semi-quantitative assessments:

The quantitative evaluation will focus on the diagnostic performance of the predicted risks, including the estimation of sensitivity, specificity, positive and negative predictive values, discrimination using the area under the ROC curve, calibration using the Hosmer–Lemeshow test, and clinical utility assessed through decision curve analysis.The semi-quantitative evaluation will consider clinicians’ perceptions of the information provided by the models. After reviewing the model’s information, they will be asked to answer four questions to assess the perceived usefulness and potential clinical impact of the predictions: (1) overall appreciation of the information (“I like it / I don’t like it”); (2) whether this information would have influenced their decision regarding corticosteroid administration (“No / Yes, I would have administered them earlier / Yes, I would have administered them later”); (3) whether it would have modified their management of hospitalization between diagnosis and delivery (“No / Yes, I would have extend the duration of hospitalization / Yes, I would have reduced it”); and (4) whether it would have changed their decision about the timing of delivery (“No / Yes, I would have indicated delivery earlier / Yes, I would have delayed delivery”).

Following this first phase, the ML training methodology will be replicated incorporating the information from the initial 100 cases, and the updated models will then be applied prospectively to the next 100 participants. This “re-training” methodology begins with a preprocessing stage, which includes missing-value imputation using MissForest, outlier removal, standardization of numerical variables with Standard Scaler, and encoding of categorical variables using OneHot and Label encoding [34]. Subsequently, model training is carried out using genetic algorithms within a multi-objective framework. These algorithms are non-deterministic, can be adaptive, and often benefit from parallel computation, enabling them to search for high-quality approximate solutions [35].

After completing recruitment of 200 patients, a final validation will be performed, formally comparing the discriminative performance of the original and retrained models using the DeLong test for paired ROC curves. Bootstrap resampling will also be considered to derive more robust confidence intervals for key performance metrics, ensuring a stable evaluation of model behavior across samples. In parallel, the semi-quantitative responses from clinicians will be compared between the two phases, providing both an objective and a subjective assessment of model performance and clinical usability.

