The development process required addressing the complexity and heterogeneity of the dataset so a structured feature–selection pipeline was implemented using genetic algorithms (GAs), an evolutionary computation technique capable of efficiently searching high-dimensional feature spaces. Two complementary strategies were applied: a mono-objective GA aimed at maximizing the F1-score of each classifier, and a multi-objective GA (NSGA-II) that simultaneously optimized predictive performance and model parsimony, favouring solutions with fewer variables to enhance clinical feasibility [31]. The three models underwent internal validation and demonstrated promising diagnostic performance (sensitivity and specificity of 70%/74%, 69%/88% and 88%/69%, respectively). The R model (K-Nearest Neighbor) included twenty-five predictive variables, the T one (Logistic Regression) included fourteen, whereas the HA (Logistic Regression) incorporated thirteen. Subsequently, simplified versions of the models were derived from the multi-objective strategy: based on only five, seven and three features, achieving a sensitivity of 60%/68%/92% and a specificity of 74%/86%/52% (Fig. 1) [30]. Although the HA model prioritizes sensitivity over specificity, this trade-off may be clinically acceptable, particularly between 30 + 0 and 33 + 6 weeks of gestation, when the maternal risks of continuing the pregnancy increase while neonatal outcomes improve rapidly with gestational age.

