**Fig. 1 Fig1:**
[figure not shown]
Overview of the machine learning models to be validated. For each model, the classification approach, the input variables used, and the results obtained during the development phase are presented. MCAPIp5_echo: Pulsatility index in the middle cerebral artery < percentile 5; GA_PE: Gestational age at preeclampsia onset; NumDrug: Number of antihypertensive administrated drugs; PIrUtA_echo: Pulsatility index of the right uterine artery; previous_PE: Preeclampsia in previous gestations; PlGF5: Angiogenic marker < percentile 5 for gestational age according to Verlohren et al. [32]; RatioScale: Clinical classification of sFlt-1/PlGF relation (0–38: normal; >38–85: suspicion of preeclampsia; >85–655: consistent with a diagnosis of preeclampsia; >655: high-risk of preeclampsia-related complications); weight: Pre-gestational weight; EFWp_echo: Customized percentile of estimated fetal weight; PIlUtA_echo: Pulsatility index of the left uterine artery; chronic_ht: Maternal chronic hypertension; mPIUtAMoM: Multiples of the median of the mean pulsatility index of the uterine arteries; sFLt195: Antiangiogenic marker > percentile 95 for gestational age according to Verlohren et al. [32]; PlGFscale: Clinical classification of PlGF

Despite these encouraging findings, external validation in a broader and more heterogeneous population is essential before these models can be considered for clinical implementation. The present study aims to address this need assessing the diagnostic accuracy, calibration, and clinical utility of the models across multiple hospitals participating in the Spanish RICORS-SAMID network.

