### Sample size estimation

We will evaluate 5 candidate predictors for the R model, 7 for the T model, and 3 for the HA model as specified in Fig. 1. Following the recommendation of having at least 10 events per predictive variable and assuming that:

Approximately 50% of women with eoPE deliver within ≤ 7 days [14], the required sample size to validate the T model is: 7 (predictive features) x 10 (events) / 0,5 (event incidence) = 140 eoPE casesApproximately 40% of women with eoPE experience any PE-related complication, and in 20% these complications include placental abruption or HELLP syndrome [30]. According to this, the required sample size to validate the R model is: 5 (predictive features) x 10 (events) / 0,4 (event incidence) = 125 eoPE cases, and to validate the HA model is: 3 (predictive features) x 10 (events) / 0,2 (event incidence) = 150 eoPE cases

This estimation assumes independence among predictor variables. However, ML techniques can identify dependencies between variables when present, which could potentially reduce the required sample size. Nonetheless, we have chosen to maintain the estimate of 200 cases, as it is the most conservative assumption and aligns with the sample size used in our previous work during model development, providing greater confidence.

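### Calibration is a stated aim, but the only method named for it is the Hosmer–Lemeshow test, which shows neither size nor direction and says little when non-significant at 100 patients

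*Protocol article*

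**What the plan says.** The Background, in the text after Fig. 1, gives the study's aim as "assessing the diagnostic accuracy, calibration, and clinical utility of the models" across hospitals. The section on the models' validation strategy then lists the quantitative measures. For calibration it names one: "calibration using the Hosmer–Lemeshow test". It names no intercept, slope, observed/expected ratio or calibration plot. Clinical utility has its own method, decision curve analysis.

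On timing, the same section states: "An analysis will be conducted after the inclusion of the first 100 participants". The retrained models are then applied to the next 100. At 200 patients the formal comparison concerns discrimination only: "formally comparing the discriminative performance of the original and retrained models using the DeLong test for paired ROC curves". On intervals the article says: "Bootstrap resampling will also be considered to derive more robust confidence intervals for key performance metrics". It does not say whether calibration is among those metrics.

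The number of groups and the degrees of freedom for the test are not stated. On the classifier, the Background says: "The R model (K-Nearest Neighbor) included twenty-five predictive variables". T and HA are described there as logistic regressions.

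**The concern.** The test answers yes or no to whether observed and expected counts differ by more than chance. It cannot say whether risks are too high, too low or too extreme, or by how much. In a small sample, a non-significant result may mean that the model is well calibrated or that the sample could not show otherwise.

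This matters here because the web application shows clinicians predicted probabilities and opens the T and HA models only above an R risk of 0.5. Retraining also follows the first validation. To learn from those 100 patients, the team needs to know whether the fault is a shift in average risk or a wrong spread, and a single p-value does not tell them.

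**Working it through.** **The plan's own figures.** The sample size section uses ten events per predictor: T 7 × 10 / 0.5 = 140; R 5 × 10 / 0.4 = 125; HA 3 × 10 / 0.2 = 150. All three reproduce. None concerns the power or precision of a calibration assessment.

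**Inputs from the article.** n = 100 at the first validation. Event rates are 40% for R, 20% for HA ("in 20% these complications include placental abruption or HELLP syndrome") and 50% for T ("Approximately 50% of women with eoPE deliver within" seven days).

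**Assumptions not in the article.** The predicted linear predictor is normal with SD 0.9 to 1.2. The test uses ten groups and, because no parameter is estimated from the validation data, 10 degrees of freedom; alpha is 0.05. A shift of 0.5 on the log-odds scale is substantial:
- A predicted 40% becomes expit(−0.405 + 0.5) = 52%.
- A predicted 20% becomes expit(−1.386 − 0.5) = 13%.

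**Simulated power at n = 100**

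| Miscalibration | Hosmer–Lemeshow | Direct test |
|---|---|---|
| Shift +0.5, 40% events | 32–34% | 58–64% (calibration-in-the-large) |
| Slope 0.5, 40% events | 29–47% | 39–54% (joint intercept and slope) |
| Shift −0.5, 20% events | 3–4% | 39–41% (calibration-in-the-large) |

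The ranges run over the assumed SD. With 1,500 data sets per setting, simulation error is at most about 1.96 × √(0.25/1500) = 2.5 points, so the figures are approximate. In the last row the model overstates a low risk. The test then divides by a variance larger than the true one, which shrinks the statistic.

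**Milder and grosser errors (SD 1.2, n = 100).**
- Slope 0.8 is detected in 12–14% of samples across the three models, and slope 0.7 in about 20%.
- An observed/expected ratio of 0.67 is detected in 91% of samples for R and 100% for T, but in 16% for HA.
- At n = 200, slope 0.7 is still detected in only 28–30%.

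**Precision of the direct measures.** The 95% interval for observed/expected, if the true value is 1, is exp(±1.96 × √((1−p)/(np))).

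| Model | n = 100 | n = 200 |
|---|---|---|
| R | 0.79–1.27 | 0.84–1.18 |
| T | 0.82–1.22 | 0.87–1.15 |
| HA | 0.68–1.48 | 0.76–1.32 |

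The simulated standard error of the slope at n = 100 is 0.25 (R), 0.24 (T) and 0.30 (HA), so its 95% interval is about ±0.5 to ±0.6.

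**If R outputs nearest-neighbour vote shares.** With equal votes, k neighbours give at most k + 1 distinct risks. In simulated samples of 100, at least one decile had zero expected variance in essentially all samples for k = 5, 50% for k = 9, 22% for k = 11 and 3% for k = 15. The share of risks equal to exactly 0 or 1 was 26% for k = 5 and 6% for k = 15. The article does not give k.

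**The case against.** Low power is mainly a sample-size limit. The direct tests reach only 39–64% in the scenarios above, and setting an omnibus test against a one-degree-of-freedom test built for a pure shift favours the latter. The comparison also depends on where the assumed spread sits. If an SD of 0.9 is placed on the true rather than the predicted linear predictor, the test detects a slope of 0.5 in about 76% of samples, against 78% for the joint test. The simulations use a continuous predictor, whereas the three HA predictors are threshold or class variables. All of this stands. The direct measures are preferable chiefly because they report size, direction and uncertainty; their gain in power is secondary.

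Four stronger readings are tempting, and the article does not support them.
- **The test misses most relevant miscalibration.** It does not miss gross errors in R and T, and the article defines no relevant size.
- **The plan uses the software default of two fewer degrees of freedom than groups.** That default would raise the false-positive rate to P(χ² with 10 df > 15.51) = 11.5% with ten groups, but the article fixes neither groups nor degrees of freedom.
- **The test cannot be used on R.** The text ties K-nearest neighbour to the 25-variable version. The classifier of the five-feature version is not given in the text, and ties are a minor matter from about k = 15.
- **A non-significant result will be declared good calibration, or the other measures fail with it.** No such rule is written. Sensitivity, specificity and predictive values check the 0.5 cut-off directly, and miscalibration lowers observed net benefit in a decision curve.

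**Conclusion.** The point holds as a weakness in a stated method. Calibration is an aim, and the one method named for it cannot describe miscalibration and has limited power at 100 patients. The clearest gap is overestimation of HA risk, where power is about 3–4% for a −0.5 log-odds shift. For a moderate shift or slope error in an R-type model it is roughly 30–47%. These figures rest on the assumed normal predictor (SD 0.9 to 1.2 on the predicted scale), ten groups and 10 degrees of freedom, and would change with the real distribution of predictions. The point is not a detail that an article leaves to an analysis plan, because the article makes the choice itself. It does not invalidate the discrimination, classification or decision-curve results.

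**What to change.** For R, T and HA, name as the main calibration results the observed/expected ratio or calibration-in-the-large and the calibration slope, each with a 95% confidence interval, plus a calibration plot. Apply this at 100 patients and at the final validation. Keep the Hosmer–Lemeshow test at most as a supplement, with degrees of freedom equal to the number of groups, since the data are external to model fitting.

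State the classifier of the simplified R model and, if it is K-nearest neighbour, k and the weighting. If R outputs vote shares, report observed/expected and the observed event rate at each distinct predicted value. Fix in advance how risks of exactly 0 or 1 are handled before any logit-based slope is fitted, because the logit is undefined there.

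No extra data are needed. The cost is a little more analysis and a few sentences of text. The intervals will be wide at 100 patients, especially for HA, and the report should say so.
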